**E-mail contact for SAE and SUSARs notification and information is:**

**[contact]**

**([name])**

Warnings and precautions

No evidence available at the time of the approval of this study protocol indicated that special warnings or precautions were appropriate, other than those noted in the provided Summary of Product Characteristics or in the IB. Additional safety information collected between IB updates will be communicated in the form of Investigator Notifications. This information will be included in the patient informed consent and should be discussed with the patient during the study as needed.

EIO Safety Committee (SC)

The SC will ensure transparent management of the safety information through investigator notifications and recommending modifications as circumstances require. Together with the clinical trial team, the SC may be involved in evaluations about the risk/benefit ratio based on new risks evidenced by SUSARs.

# 11. STUDY MONITORING

## 11.1 Data Management

We will conduct the trial according to the ICH Good Clinical Practice (GCP) guidelines. Keeping accurate and consistent records is essential to a cooperative study.

The IEO Data Management Office will be responsible of the study database development and data management. IEO Data Management Office, Direzione Scientifica, Istituto Europeo di Oncologia -[name] - T [name] F [name] M [name]

Data for this study will be collected in a REDCap® (Research Electronic Data Capture) database. REDCap was developed specifically around HIPAA-Security guidelines. More information about the consortium and system security can be found at <http://www.projectredcap.org/>. REDCap is a secure web platform for building and managing online databases and surveys. REDCap's streamlined process for rapidly creating and designing projects offers a vast array of tools that can be tailored to virtually any data collection strategy. REDCap provides an intuitive user interface that streamlines project development and improves data entry through real-time validation rules (with automated data type and range checks). REDCap also provides easy data manipulation (with audit trails for reporting, monitoring and querying patient records) and an automated export mechanism to common statistical packages (SPSS, SAS, Stata, R/S-Plus). Investigators who have received appropriate institutional research approval (i.e., Institutional Review Board or Institutional Ethics Committee) will be given a web link with a survey where they can enter data about their specific patients. Guidelines about the data collection and to properly enter the data will be developed. The Promoter/Study Coordinator Centre is the legal owner of the collected data and has the right to manage it (including the data collected by the centers involved) in the case of a multi-site study, the sharing of data to any satellite centers is at the discretion of the Coordinator Centre under existing contractual agreements the regulation regarding protected health information (PHI) is also valid in Italy: it is therefore not possible to enter sensitive data of the subjects enrolled in the study or any other data (such as hospital codes/labels/SDO) that can lead to their identity; that's why when a subject is inserted into the platform, the system assigns her/him a unique identifier. The id/name-last name code decoding is the responsibility of the PI of each experimental center (and should not be shared with the Coordinator Center). Each experimental center will then be the only one to be able to decode the IDs assigned to the subjects managed by its center.

Investigators will access the medical records of their patients, enter required data into the database. The protected health information will not be reused or disclosed to any other person or entity, except as required by law, for authorized oversight of the research project. Future research, that is not defined in this protocol, wishing to access the REDcap database will need institutional review board/ethic review board approval before obtaining access to the REDcap database.

## 11.1.1 Data Protection

Information technology systems used to collect, process, and store study-related data are secured by technical and organizational security measures designed to protect such data against accidental or unlawful loss, alteration, or unauthorized disclosure or access. In the event of data security breach, appropriate mitigation measures will be implemented.

## 11.1.2 Protocol Deviations

The investigator should document and explain any protocol deviations. The investigator should promptly report any deviations that might have an impact on participant safety and data integrity to the Sponsor and to the IRB/EC in accordance with established IRB/EC policies and procedures. The Sponsor will review all protocol deviations and assess whether any represent a serious breach of Good Clinical Practice guidelines and require reporting to health authorities.

## 11.2 Registration/Randomization

**Identification of participants**

According to good clinical practice (GCP) guidelines and current legislation, patients have a right to privacy. Therefore, case report forms (CRF) or any other document related to the study will not contain subject names. Subjects will be identified by a unique code attributed at the moment of study inclusion.

The local data manager will maintain the internal registry for the identification of all subjects participating in this study. The registry will contain:

- name and surname of the participant;
- medical record number;
- screening ID
- unique identification code;
- date of birth;
- date of inclusion in the study/signed informed consent.
- reason of ineligibility or refusal

Additionally, all institutional measures for the safeguard of patient privacy will be implemented.

Screening:

All potentially eligible participant will be contacted to propose the study, to this patient will be assigned a temporary ID number and only to the one will be actually sign the inform consent will receive the unique identification code

Randomization:

Randomization will be performed using REDCAP platform.

Participants will be randomized to one of the four intervention arms once eligibility has been verified at the site level, eligibility has been confirmed by the site PI or his designee, eligibility CRF has been entered into the DB web application. Once eligibility has been verified and confirmed, the allocated arm will be generated by the database and assigned to the participant. Refer to Section 12.2 for details of randomization.

Appropriate CRFs must be completed for any participant who signs an informed consent. If a consented participant is a screen failure and deemed ineligible, the following CRFs must be completed: 1) Screening CRF 2) Registration CRF; 3) Randomization CRF with the eligibility box checked “no”, 4) the Inclusion and Exclusion CRFs showing why the participant is ineligible, 5) the Off-Study CRF, 6) the Concomitant Medication CRF and 7) the Verification CRF. If no Concomitant Medications were assessed by the time the participant is deemed ineligible, the “NONE” box will be checked. All participants who sign an informed consent must formally go off study. All participant registration information will be entered into DB.

## 11.3 Case Report Forms

Participant data will be collected using protocol-specific case report forms (CRF). The approved CRFs will be used to create the electronic CRF (e-CRF) screens in the REDCAP application. Site staff will enter data into the e-CRF.

## 11.4 Source Documents

Source documentation will include only those documents containing original forms of data, including clinic charts, shadow files, hospital charts, questionnaires and physician notes. Data recorded directly on the CRFs designated as source documents (i.e., no prior written or electronic record of data) will be considered source data. All other data recorded on the CRFs will not be considered source documentation. Self-reported questionnaires and diaries will be considered source data.

## 11.5 Record Retention

Clinical records for all participants, including CRFs, all source documentation (containing evidence to study eligibility, history and physical findings, laboratory data, results of consultations, *etc*.), as well as IRB records and other regulatory documentation will be retained by the Investigator in a secure storage facility. The records should be accessible for inspection and copying by authorized persons of the Italian Ministry of Health representative and Italian Agency of Drug (AIFA), and to study monitors.

In compliance with the ICH/GCP guidelines, the investigator/institution will maintain all eCRFs and all source documents that support the data collected from each subject, as well as all study documents as specified in ICH/GCP Section 8, Essential Documents for the Conduct of a Clinical Trial, and all study documents as specified by the applicable regulatory requirement(s).

The investigator/institution will take measures to prevent accidental or premature destruction of these documents. Essential documents must be retained until at least 25 years after the last approval of a marketing application in an ICH region and until there are no pending or contemplated marketing applications in an ICH region or until at least 15 years have elapsed since the formal discontinuation of clinical development of the investigational product. These documents will be retained for a longer period if required by the applicable regulatory requirements or by an agreement with the sponsor. It is the responsibility of the sponsor to inform the investigator/institution as to when these documents no longer need to be retained.

If the responsible investigator retires, relocates, or for other reasons withdraws from the responsibility of keeping the study records, custody must be transferred to a person who will accept the responsibility. The sponsor must be notified in writing of the name and address of the new custodian. Under no circumstance shall the investigator relocate or dispose of any study documents before having obtained written approval from the sponsor. If it becomes necessary for the sponsor or the appropriate regulatory authority to review any documentation relating to this study, the investigator must permit access to such reports

# 12. STATISTICAL CONSIDERATIONS

## 12.1 Statistical Plan

*Sample size considerations*

Main objective

Given the results found in our previous studies^18, 57^, we considered as main endpoint SHBG (nmol/L) post treatment, which has been shown to be associated with risk of first cancer or cancer recurrence. Taking into account a drop-out rate of 10% we will have to enroll a total of 200 subjects. In fact, a sample size of overall 180 patients (90 per arm) achieves 80% power to detect a difference of 15 points between the null hypothesis that means of SHBG (nmol/L) post treatment are in both arms 70 and the alternative hypothesis that the mean in the tamoxifen arm is 85, with an estimated group standard deviation of 35 and with a significance level (alpha) of 5% using a two-sided two-sample t-test.

Secondary objectives

In order to investigate the effect of caloric restriction on biomarkers, we will subdivide each arm in two further groups: with and without caloric restriction, leading to a 4 arms design (45 patients per arms). Adjusting for multiple testing will be carry out for all secondary objectives that have an explorative nature.

## 12.2 Randomization/Stratification

In order to keep as low as possible the imbalance in treatments a stratified blocked randomization strategy will be used considering only the relevant prognostic factors. Participants will be stratified according to center and diseases status (healthy high risk versus affected).

## 12.3 Statistical analysis

Subject characteristics, information on lifestyle risk factors, diet and serum biomarkers at baseline will be summarized with descriptive characteristics. Median and interquartile range for continuous variables and absolute and relative frequencies for categorical variables will be presented by arms. Kruskal-Wallis test and Chi-square test (Fisher exact test for sparse data) will be used to assess differences at baseline between arms. Comparisons by affected versus high risk subjects of baseline serum biomarkers will be also carried out using Wilcoxon sum-rank test. We will employ linear regression models to investigate the associations between Tamoxifen treatment, LI and ICR with both post-treatment and changes from baseline of SHBG and all serum biomarkers. We will check whether we need to control for confounding factors and the baseline values. The normality of the models’ residuals will be verified by graphically checking the empirical distribution of the residuals and by looking at Q-Q plots, which compare the cumulative distribution of our data with that of the normal distribution. With multivariate logistic regression, serum biomarkers will be also investigated as categorical variables considering different cut-offs.

To limit the risk of technical bias and take into account the compositional nature of microbiome data, the normalized taxa abundances will be first transformed with the Centred Log-Ratio (CLR) transformation. The most discriminative taxa associated with treatment arms will be selected by using variable selection approaches adapted for compositional data, like Sparse Least Square – Discriminant Analysis (sPLS-DA) and Coda-LASSO. Multivariate linear regression models will be performed to estimate the association between Tamoxifen, LI, ICR and post-treatment clr-abundances of taxa, adjusting for confounders. Associations between post-treatment taxa and consumption of specific groups of foods will be also investigated. The level of physical activity will be quantified with the IPAQ questionnaire. Three categories of physical activity (Low, Moderate, High) will be calculated for each patient following the IPAQ scoring protocol^66^. For QoL assessment, we will analyze the four domains of MenQoL questionnaire: vasomotor, psychosocial, physical and sexual. The overall score of each domain will be calculated by dividing the sum of the domain’s items by the number of items within that domain. Higher domain scores will indicate worse QoL. Associations of the four domains with treatment, LI, ICR and taxa abundances will be estimated considering both post-treatment evaluations (at 3 months and 6 months) and changes from baseline. Multivariate linear or logistic regression will be implemented according to whether the four domains will be analyzed as continuous scales or categorized into classes. The interplay among treatment, serum biomarkers, species (normalized data) associated with treatment arms, diet and QoL will be investigated first with unsupervised methods, like networks based on Spearman’s rank Correlation Coefficient and Canonical Correspondence Analysis (CCA), then with supervised methods for data integration, like block Sparse Least Square-Discriminant Analysis (sPLS-DA) and priority-LASSO hierarchical approaches. To estimate the role of *microbiome* as mediator of treatment arms on SHBG and other biomarkers changes and to investigate its role in mediating the effect of treatments on side effects and QoL, we will perform a mediation analysis based on a counterfactual framework approach. The microbial composition of each patient will be summarized with methods of dimensionality reduction like Principal Component Analysis (PCAPathways data will be preprocessed and analyzed as described for the taxonomic data.

The primary analysis will employ an intention-to-treat approach, which includes all participant irrespective of compliance. An according-to-protocol subgroup analysis will be restricted to women who are “compliant”, such as participants who have taken ≥ 75% of the pills, for thus randomized to tamoxifen and ≥ 75% of the days with the respected caloric restriction, by the reported diary.

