**Main aim**

Effect of Tam vs LI:

Arm 1 and 2 vs Arm 3 and 4

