# 8. CRITERIA FOR EVALUATION AND ENDPOINT DEFINITION

## 8.1 Primary Endpoint

The main endpoint of the study will be serum concentrations (nmol/L) of SHBG after 6 months of intervention. We expect to obtain a difference of 15 points comparing the two low dose tamoxifen arms with the two other arms that include lifestyle intervention (step counter), with or without intermittent-caloric restriction^57, 58^. The measurement will be centralized at the Division of Cancer Prevention and Genetics at the IEO.

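### Whether the primary 6-month SHBG comparison is adjusted for baseline SHBG depends on an undefined check, and the stratification factors are not placed in the model

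*Protocol*

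**What the plan says.** The endpoint and the contrast are fixed. Section 8.1: "The main endpoint of the study will be serum concentrations (nmol/L) of SHBG after 6 months of intervention". The Schema gives the main aim as "Arm 1 and 2 vs Arm 3 and 4", that is, low-dose tamoxifen (LDT) against lifestyle intervention (LI), each pooled over intermittent caloric restriction (ICR). Section 12.1 sizes the trial for 90 evaluable women per pooled group "with a significance level (alpha) of 5% using a two-sided two-sample t-test", and says that this "achieves 80% power to detect a difference of 15 points".

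The model is not fixed. Section 12.3 plans linear regression for SHBG, both as the post-treatment value and as change from baseline, and then says: "We will check whether we need to control for confounding factors and the baseline values". It does not say what the check is, when it is made or which covariates are candidates.

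Section 12.2 stratifies randomisation by centre and disease status and treats these as the relevant prognostic factors. No section says that they enter the primary model. Section 9.1 schedules serum at baseline, three and six months, so baseline SHBG will be available.

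**The concern.** In a randomised trial, the reason to adjust for the baseline value of the outcome is precision. That reason is known before the trial starts and does not depend on anything found in the data. A rule that makes adjustment conditional on an unspecified check has two costs.

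- The precision in a measurement already taken may go unused.
- The main test can take two forms, adjusted and unadjusted, and the protocol does not say which one carries the 5% error rate.

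The same reasoning applies to the strata. Factors that restrict the randomisation and are held to be prognostic belong in the model, and here they are not mentioned in it.

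**Working it through.** **Inputs from the protocol (section 12.1):** 90 per group, difference 15 nmol/L (85 against 70), SD 35, two-sided alpha 5%, drop-out 10%.

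**Assumed:** the correlation r between baseline and 6-month SHBG. The protocol gives no figure, so a range of 0.3 to 0.8 is used.

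**1. The plan's own figures.** Standard error of the difference = 35 × √(2/90) = 5.217. Ratio = 15 / 5.217 = 2.875. Normal-approximation power = Φ(2.875 − 1.960) = 82.0%; the exact noncentral t gives 81.6%. The exact t-test needs 87 per group for 80% power, so 90 is slightly generous. Enrolment: 180 / 0.9 = 200. The stated design reproduces.

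**2. Always adjusting for baseline.** Residual SD = 35 × √(1 − r²). Standard error = residual SD × √(2/90). Power = Φ(15/SE − 1.96). Half-width of the 95% interval = 1.96 × SE.

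| r (assumed) | Residual SD | SE | Power | Half-width (nmol/L) |
| --- | --- | --- | --- | --- |
| unadjusted | 35.00 | 5.217 | 82.0% | 10.2 |
| 0.3 | 33.39 | 4.977 | 85.4% | 9.8 |
| 0.5 | 30.31 | 4.518 | 91.3% | 8.9 |
| 0.7 | 24.99 | 3.726 | 98.1% | 7.3 |

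The few degrees of freedom used by the covariates are ignored; with 180 women this is negligible. No gain is credited to centre or disease status, because the protocol gives nothing from which to estimate it.

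**3. The open choice between adjusted and unadjusted.** Under the null hypothesis, the two test statistics are approximately standard normal with correlation √(1 − r²). The chance that at least one of them exceeds 1.96 in absolute value is:

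| r (assumed) | Correlation of the two tests | Type I error if the smaller p-value is reported |
| --- | --- | --- |
| 0.3 | 0.954 | 6.4% |
| 0.5 | 0.866 | 7.3% |
| 0.7 | 0.714 | 8.3% |
| 0.8 | 0.600 | 8.7% |

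A simulation of 20,000 null trials per setting, with 90 per group, agrees: 6.5% at r = 0.3 and 8.5% at r = 0.8. Either analysis alone, fixed in advance, keeps about 5%.

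**The case against.** The strongest reply is that the essentials are settled (endpoint, contrast, alpha, intention to treat), that unadjusted power is adequate, and that a statistical analysis plan, not shown here, may name the covariates before any data are examined. Much of this stands. It does not dispose of the point, because the protocol is not silent: it states a conditional rule for adjustment, and a later plan that fixed ANCOVA would have to override it.

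Four stronger readings are tempting, and the protocol does not support them.

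- *The primary result could be a change-score analysis.* A reader might infer this from the reference in section 12.3 to both forms of outcome. A best-of-three choice would then carry an error of about 9% to 10%. But the Schema and sections 8.1 and 12.1 fix the 6-month level as primary, and section 8.2 lists change in SHBG as secondary. Only the adjusted or unadjusted choice is open.
- *Baseline tests decide the covariates.* Section 12.3 does plan them: "Kruskal-Wallis test and Chi-square test (Fisher exact test for sparse data) will be used to assess differences at baseline between arms". They belong to the description of participants, and nothing links them to covariate choice.
- *The model will be chosen after the results are seen.* No timing is stated. The text leaves this possible; it does not plan it.
- *The trial is underpowered.* It is not. The unadjusted comparison meets the stated 80%.

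**Conclusion.** The point holds in a limited form. The primary SHBG model is not fixed with respect to baseline SHBG, and the stratification factors are absent from it.

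The forgone gain over the unadjusted analysis is about 3 points of power at r = 0.3, 9 at 0.5 and 16 at 0.7, with intervals about 5%, 13% and 29% narrower. These sizes rest on an assumed correlation and on the plan's SD of 35. The 6.4% to 8.7% type I error arises only if the more favourable of the two analyses is reported. It measures what the wording allows and does not predict what the investigators will do. The effect of adding centre and disease status cannot be quantified from the protocol.

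This should be fixed, and settled before outcome data are examined. It does not undermine the design or the sample size.

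**What to change.** For the primary analysis, replace the conditional sentence in section 12.3 with: *The primary analysis is a linear model for 6-month SHBG on LDT vs LI (Arms 1+2 vs 3+4) and ICR assignment, always adjusted for baseline SHBG, centre and disease status.* Label the unadjusted comparison as supportive. Keep change from baseline in SHBG as the secondary endpoint it already is.

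The cost is one sentence in the protocol, carried into the statistical analysis plan. It needs no extra participants, visits or samples, because baseline SHBG and both strata are already collected.

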## 1.2 Secondary Objectives

The secondary aims are:

-to verify whether ICR significantly modulates main and secondary endpoints such as HOMA-index, immune and inflammatory markers, lipid profile, Adiponectin/Leptin (A/L) ratio, quality of life (QoL), Body mass index (BMI), fat body composition, safety and toxicity;

-to verify whether LDT significantly modulates secondary endpoints, such as HOMA-index, immune and inflammatory markers, lipid profile, A/L ratio, QoL, BMI, fat body composition, safety and toxicity;

-to investigate differences in microbiome composition by arms and the effect of changes in microbiome on QoL taking into account circulating biomarkers, cytokines, immune modulators and inflammatory proteins in serum;

- to investigate MD (Mammographic Breast Density) changes by LDT vs LI, with or without ICR. This aim will be performed in a subgroup of participants (not all the participants will undergo mammography due to younger age).

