# 3. STUDY DESIGN

The TOLERANT (Low dose **T**am**O**xifen and **L**if**E**style changes for b**R**east c**AN**cer preven**T**ion) study is a randomized four-arm phase II intervention trial that will enroll 200 participants at high risk of breast cancer in four Italian centers (Milan, Genoa, Padua and Naples).

Potentially eligible women will be informed about the study and will provide signed informed consent before participation. At baseline, participants will be screened to confirm eligibility and will be randomly assigned (1:1:1:1) to one of the four intervention arms (Figure 1):

*Arm 1:* Low dose Tamoxifen (LDT) i.e 10 mg every other day;

*Arm 2:* Low dose Tamoxifen (LDT) + Intermittent Caloric Restriction (ICR);

*Arm 3:* Lifestyle intervention (LI) using a step counter;

*Arm 4:* Lifestyle intervention (LI) using a step counter + Intermittent Caloric Restriction (ICR).

Figure 1

[figure not shown]

Stratification: center and disease status (high risk vs previous IEN)

A schematic description of the study procedures is reported in figure 2.

Figure 2

[figure not shown]

Trained staff including dietitians/nutritionists will provide advices based on international and national recommendations (WCRF.2018; CREA, 2019 https://www.crea.gov.it/web/alimenti-e-nutrizione/-/linee-guida-per-una-sana-alimentazione-2018) at baseline to all participants. Depending on intervention allocation, dietitians/nutritionists will provide a caloric restriction plan to Arm 2 and 4. Participants included in Arm 3 and 4, will receive a step counter that encourages both increased physical activity and decreased sedentary time. Depending on intervention allocation, tamoxifen pills will be provided (Arm 1 and 2). All participants will receive a calendar in order to record drug intake, ICR dates and weekly step counter where appropriate. The study interventions will last 6 months.

To maintain high compliance during the 6-month intervention phase (T2, T3 and T5) participants will receive phone calls in order to monitor and reinforce adherence to the proposed intervention, and to record possible adverse effects. At visit T1, T4 and T6 blood samples will be collected, anthropometric measures, study questionnaires will be collected. Stool will be collected at T1 and T6. Depending on local availability, a sub-sample of participants will be invited to do DEXA for adipose tissue evaluation.

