## 7.5 Three-month visit

Fasting blood will be drawn for glycemia and blood circulating biomarkers. A stool kit collection will be provided to the participant, to be collected at the final study visit. Date of last menses will be recorded.

Physical exam, vital signs, anthropometric measurement including BIVA, quality of life, food habit and physical activity will be assessed by self-administered questionnaires.

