## 9.2 Stool

Fecal samples will be collected for microbiome analysis at baseline and final visit. Specimens will be collected by patients at home and transported in a collection tube prefilled with preservative liquid, which stabilizes nucleic acids preventing them from being degraded up to 6-8 weeks at room temperature.

Specimen collection kits for storage of fecal samples will be provided by the European Institute of Oncology in Milan.

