
## 9.4. Study specimen and procedure management

Planned analysis of circulating and other biomarkers will be determined by specialized laboratories/departments as outlined below:

| **Specimen (amount)** | **Laboratory** |
| --- | --- |

| **Serum: 6 aliquots (2 mL each) per time point**  For all circulating biomarkers  At baseline, 3 months, and 6 months (or study cessation) | [name], PhD  Division of Cancer Prevention and Genetics  European Institute of Oncology |
| --- | --- |
| **Stool: 1 aliquot per time point**  Microbiota analysis at baseline and 6 months  **Whole blood 1 aliquot per time point**  Immune-gene expression profile | Istituto Nazionale Tumori G. Pascale, Naples |
| **Mammograms***  Baseline and final images will be recorded to mammographic analysis | [name] MD  Department of Breast Radiology,  European Institute of Oncology |

*Only in a subgroup of participants

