**ISTRUZIONI PER LA COMPILAZIONE**

Ogni domanda del questionario si presenta come negli esempi qui sotto:

Nessun Moltissimo

fastidio 0 1 2 3 4 5 6 fastidio

SUDORI NOTTURNI ❒ ❒ - 0 1 2 3 4 5 6

No Sì

Indichi se ha avuto o meno questo problema durante *le ultime 4 settimane*.

SE *NON HA* AVUTO QUESTO PROBLEMA:

Segni "No"

SUDORI NOTTURNI 🗷 ❒ - 0 1 2 3 4 5 6

No Sì

Passi alla domanda successiva.

SE *HA* AVUTO QUESTO PROBLEMA:

Segni "Sì", poi faccia un cerchietto intorno al numero che indica quanto *fastidio* le ha causato questo problema

SUDORI NOTTURNI ❒ 🗷 - 0 1 2 3 4 5 6

No Sì

Passi alla domanda successiva.

Questo questionario è strettamente riservato. Il suo nome non verrà associato in alcun modo alle sue risposte. Comunque, se per qualsiasi motivo non desiderasse rispondere a una domanda, la preghiamo di saltarla e di passare a quella successiva.

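### With stool taken only at baseline and 6 months, the planned microbiome mediation analysis cannot address earlier side effects or 3-month QoL, and cannot establish direction for 6-month outcomes

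*Protocol*

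**What the plan says.** **The causal aim.** Section 1.2 lists as a secondary aim "the effect of changes in microbiome on QoL". Section 12.3 plans a counterfactual mediation analysis with the microbiome as mediator of treatment effects on SHBG and other biomarkers, and also to "investigate its role in mediating the effect of treatments on side effects and QoL". It names no outcome time point for that analysis. Separately, it relates the four MenQoL domains to treatment, LI, ICR and taxa abundances, "considering both post-treatment evaluations (at 3 months and 6 months) and changes from baseline".

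**The mediator.** The stool schedule is stated consistently. Section 3: "Stool will be collected at T1 and T6". Section 9.2: "Fecal samples will be collected for microbiome analysis at baseline and final visit". The table in section 9.4: "Microbiota analysis at baseline and 6 months". At month 3 only the kit changes hands (section 7.5): "A stool kit collection will be provided to the participant, to be collected at the final study visit".

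**The outcomes.** The schedule of events in section 7.1 has adverse events at T2, T3, T4, T5 and T6, and the QoL questionnaire at T1, T4 and T6. The MenQoL instructions in Appendix E open with "Indichi se ha avuto o meno questo problema durante" and then name the last four weeks. SHBG and the other serum biomarkers are measured at T1, T4 and T6.

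**The concern.** An indirect effect through a mediator is interpretable only if the mediator comes before the outcome. The baseline stool sample precedes randomisation, so it cannot carry a treatment effect. That leaves one usable mediator value, at T6, which is later than some of the outcomes and level in time with the rest.

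The protocol itself gives reasons to expect influence in the other direction. Section 2.2 says that women with more menopausal symptoms tend to engage less in healthy behaviour, and that taxa are associated with diet and lifestyle. Sections 5.4 and 7.7 allow a side effect to end the intervention while endpoint data are still collected where possible. For such a woman the T6 microbiome may reflect the stopping that the side effect caused.

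At stake is interpretation. A path from treatment to symptoms to behaviour to microbiome could appear as microbiome mediation, and the data could not tell the two apart.

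**Working it through.** **Step 1: the plan's own figure.** The protocol gives no power or size for the mediation analysis. Its only such figure is for the primary SHBG comparison (section 12.1). With 90 per pooled group, difference 15, SD 35 and a two-sided 5% t-test, power is 81.6% against the stated 80%, and 180 / (1 − 0.10) = 200. That figure reproduces, and this point does not touch it.

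**Step 2: timing, side by side.**

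| Outcome | When recorded | Relation to the T6 stool sample |
| --- | --- | --- |
| Side effects at T2, T3, T4, T5 | about months 1, 2, 3, 5 | outcome earlier by about 5, 4, 3 and 1 months |
| QoL at T4 | month 3, covering the previous 4 weeks | outcome earlier by about 3 months |
| QoL at T6 | month 6, covering the previous 4 weeks | essentially concurrent; order undetermined |
| SHBG and other biomarkers at T6 | month 6 | essentially concurrent; order undetermined |

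For the first two rows the order is reversed. For the last two it is not fixed by the design.

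**Step 3: what pure reverse causation would produce.** Assume no true mediation. Let T be treatment, Y the outcome and M the microbiome summary:

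- Y = tT + u, with var(u) = 1
- M = bY + e, with var(M given T) = 1, so b equals r, the partial correlation of M and Y given T
- effect of T on M: r × t
- coefficient of M in the regression of Y on M and T: r
- apparent indirect effect: r × t × r = r²t
- total effect: t, so the apparent mediated share is r²

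For assumed r = 0.3, 0.4 and 0.5 the share is 0.09, 0.16 and 0.25. The true share is zero by construction.

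**Step 4: how often a test would declare mediation.** The simulation used 180 women (90 v 90) and 4,000 runs per setting. Treatment changed 3-month QoL, 3-month QoL changed the 6-month microbiome, and the microbiome did not affect QoL. Mediation was declared when both paths were significant at two-sided 5%. Entries are for 3-month QoL as the outcome.

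| Assumed standardised treatment effect on QoL | r = 0 | r = 0.2 | r = 0.3 | r = 0.4 | r = 0.5 |
| --- | --- | --- | --- | --- | --- |
| 0.3 | 0.2% | 5.6% | 9.2% | 12.6% | 16.7% |
| 0.5 | 0.3% | 7.2% | 16.7% | 26.2% | 39.2% |
| 0.8 | 0.3% | 14.1% | 35.1% | 56.9% | 75.2% |

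For 6-month QoL, with an assumed persistence of 0.6 from month 3, the rates for r from 0.2 to 0.5 ran from 2.7% to 73.9%. The effect sizes, r and the persistence are all assumptions; the protocol gives none of them.

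**The case against.** The strongest reply is that section 12.3 leaves more open than a quick reading suggests. Several parts of it stand.

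- **Which taxa go with 3-month QoL.** A reader might infer that 6-month taxa will be paired with 3-month QoL. The text does not say so. It writes of post-treatment taxa in neighbouring sentences but not in this one, and baseline taxa against 3-month QoL would be in the right order. That sentence also promises associations, not mediation.
- **Order at 6 months.** A reader might infer that no planned pairing can have the right order. Stool is collected at home, in preservative stable for 6 to 8 weeks (section 9.2), with the kit supplied at month 3. The sample may precede the T6 blood draw and questionnaire, but the interval is not specified. The order is undetermined, not shown to be wrong.
- **Direction of the diet link.** Section 2.2 reports an association between taxa and diet, and raises the microbiome as a possible mediator of diet on cancer risk. It does not say that taxa follow diet.
- **Partial safeguards.** Diet, physical activity and QoL are all measured at T1, T4 and T6, so a path from symptoms through behaviour can be examined in part.
- **Standing of the analysis.** Section 12.1 calls the secondary objectives explorative.

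A statistical analysis plan could also restrict mediation to 6-month outcomes. That would remove the reversed pairings but leave concurrency. It could not supply a microbiome value from between randomisation and the T2 to T5 side effects or 3-month QoL, because the protocol fixes the sampling times.

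**Conclusion.** The point holds in a limited form. For side effects with onset recorded at T2 to T5 and for 3-month QoL, the only post-randomisation microbiome value comes after the outcome, so no valid mediated effect can be estimated. For 6-month QoL, SHBG and other biomarkers, mediation and reverse causation cannot be told apart. The first conclusion rests only on the schedule; the second also on the unspecified interval between home stool collection and the visit.

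Three stronger statements are tempting and unsupported:

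- That reverse causation *would* be reported as mediation. It could be; the size depends on an unknown path from symptoms to microbiome.
- That the 9% to 25% share estimates the bias in this trial. It assumes zero true mediation, pure reverse causation and correlations that the protocol does not give.
- That most side effects precede the mediator. No data support this, and side effects are also recorded at T6.

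The analysis is secondary and exploratory, and the primary endpoint is unaffected. This is a cheap improvement.

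**What to change.** In section 12.3:

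- Exclude from the mediation analysis 3-month QoL and side effects with onset before the T6 stool sample. Onset dates are already required by section 10.1. The rule also needs the date of home stool collection, so sites should record it if the manual of procedures does not already ask for it.
- For 3-month QoL and early side effects, use only baseline taxa as predictors, not T6 taxa.
- For 6-month QoL, SHBG and the other biomarkers, relate the T1 to T6 change in microbiome to the change in outcome, adjusted for arm and baseline, and report it as an association. Alternatively, keep the indirect-effect estimate but label it exploratory, with direction not established.

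In section 1.2, restate the aim as *the association of changes in microbiome with QoL*.

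The cost is wording in two sections and, if not already collected, one date. No samples or visits are added. The downside is small: the trial gives up a mechanistic claim in a secondary exploratory analysis.
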